### 2.6 Participant timeline

Fifty-two weeks of medical intervention will be followed by another 52 weeks of observation, for a total of 104 weeks. The time points for the measurements are as follows: screening (0 days), 4 ± 3 days, 12 ± 5 days, 24 ± 5 days, 52 ± 5 days, 78 ± 5 days and 104 ± 5 days. During the trial and follow-up, participants will be observed and evaluated via clinical and/or imaging examinations.

### 2.7 Sample size

As this trial primarily assessed feasibility on RA prevention by TCM, sample size was not strictly predetermined. We initially allocated 30 participants per group with an additional 20% potential dropouts, resulting in a total of 72 recruitment. Nevertheless, we provide a formal calculation for reference purposes.

According to previous study (35), we assumed that RA incidence would be 20.0% in the FA group and 37.5% in the placebo group. This allocation ensured an power of over 80%. Calculation was in accordance with the formula of Chow (36) as follow:

$$\text{N}=\frac{{\left({\text{Z}}_{\alpha }+{\text{Z}}_{\beta }\right)}^{2}\,\left[{\text{P}}_{0}\,\left(1-{\text{P}}_{0}\right)+{\text{P}}_{1}\,\left(1-{\text{P}}_{1}\right)\right]}{{\left(\varepsilon +\delta \right)}^{2}}$$

Note: *N* is the sample size of each group. P_0_ and P_1_ are the RA incidence in the FA group and placebo group, respectively. For a two-sided test, α = 0.05, β = 0.2, 1−β = 0.8, Z_α_ = 1.96, Z_β_ = 0.84. The superiority margin δ = 0.15. And ε is the practical margin.

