### 2.8 Randomization and blinding

The randomization will be performed via the block randomization method by using the PROC PLAN procedure of SAS V9.4, which is administered by the Key Unit of Methodology in Clinical Research (KUMCR) at the GPHCM. According to the sample size estimate, 72 patients will be included in this study and randomly divided into two groups at a 1:1 ratio. To avoid wasting random numbers, two extra random numbers were added, and the adjusted random number is 74. Once the sample size reaches 72, patient enrolment will cease, even though there might still be unused random numbers at that point. After informed consent is obtained from participants who meet the eligibility criteria, clinicians can access the online random allocation system to procure the allocation results and immediately implement the intervention measures. When multiple patients are randomly assigned on the same day, the application procedure should be performed one by one. The patients, clinicians and investigators of this trial, including study assistants and statisticians, are blinded to the assignment. Unblinding is permitted in an emergency if a SAE occurs or if the intervention must be known for rescue.

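### The stated power of over 80% is wrong: at the assumed rates, power is about 32–40%, and 80% appears only when the 15-point margin is added to the expected difference

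*Protocol article*

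**What the plan says.** Section 2.7 explains that the trial mainly assesses feasibility and that its size was not strictly fixed in advance. It then gives the numbers: "We initially allocated 30 participants per group with an additional 20% potential dropouts, resulting in a total of 72 recruitment". It continues: "Nevertheless, we provide a formal calculation for reference purposes".

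The inputs to that calculation are:
- Rates: "we assumed that RA incidence would be 20.0% in the FA group and 37.5% in the placebo group".
- Error rates: "For a two-sided test, α = 0.05, β = 0.2, 1−β = 0.8", with Z values 1.96 and 0.84.
- Margin: "The superiority margin δ = 0.15".
- Remaining term: "And ε is the practical margin", with no number.

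The printed formula has (ε + δ)² in its denominator. The conclusion carries no qualification: "This allocation ensured an power of over 80" per cent. Section 2.8 refers back to the calculation: "According to the sample size estimate, 72 patients will be included in this study".

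Section 2.9.2 plans a log-rank comparison of the primary outcome with Kaplan–Meier curves. It makes all tests two-sided at 0.05 and judges superiority with a 95% confidence interval.

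**The concern.** A difference of 17.5 points between two proportions of this size normally needs roughly 100 participants per group for 80% power, not 30. A margin that must be exceeded to claim superiority makes a trial larger, yet here it makes the trial smaller. Adding a positive margin to the expected benefit sizes a test of whether FA is less than 15 points worse than placebo. That is a non-inferiority question. It does not fit the name given to δ, and it does not fit the two-sided log-rank superiority comparison in section 2.9.2.

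What is at stake is how a null result is read. At the stated power, a non-significant log-rank test would count against the assumed effect. At the actual power, the trial has about a 60–68% chance of missing that effect even if it is real. A later trial planned from this one would also inherit the formula.

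**Working it through.** **Inputs.** From section 2.7: rates 0.200 and 0.375, Z values 1.96 and 0.84, δ = 0.15, and 30 per group recruited as 36. Assumption: ε = 0.375 − 0.200 = 0.175, because no value is printed.

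**Step 1: reproduce the plan's figure.**
- Variance term: 0.2 × 0.8 + 0.375 × 0.625 = 0.394375.
- Numerator: (1.96 + 0.84)² × 0.394375 = 7.84 × 0.394375 = 3.0919.
- With the margin added: 3.0919 / 0.325² = 29.3, rounded up to 30 per group.
- Power at 30 per group: standard error √(0.394375/30) = 0.1147, and Φ(0.325/0.1147 − 1.96) = 80.9%.

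This matches both the 30 and the claim of over 80%.

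**Step 2: change only the treatment of the margin.**

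| Denominator | N per group |
|---|---|
| (0.175 + 0.15)², as printed | 29.3 |
| 0.175², ordinary superiority | 101.0 |
| (0.175 − 0.15)², superiority by 15 points | 4,947 |

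Reading ε as signed (−0.175) in the printed formula gives the last row, so it does not rescue the claim. With pooled variance under the null, ordinary superiority needs 104 per group instead of 101.

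**Step 3: power for ordinary superiority, two-sided 0.05.** For the log-rank test, assume proportional hazards and that both rates are cumulative over the same follow-up. Then HR = ln(0.8)/ln(0.625) = 0.475. Expected events are 30 × (0.200 + 0.375) = 17.25, or 36 × 0.575 = 20.7.

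| Method | 30 per group | 36 per group |
|---|---|---|
| Two proportions, pooled z | 31.9% | 37.2% |
| Two proportions, unpooled z | 33.2% | 38.7% |
| Log-rank, Schoenfeld | 34.0% | 39.5% |
| Log-rank, Freedman | 31.5% | 36.7% |
| Log-rank, simulated (6,000 runs, exponential times) | 32.9% | 38.2% |

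Example (Schoenfeld, 30 per group): Φ(√17.25/2 × |ln 0.475| − 1.96) = Φ(−0.41) = 34.0%. For 80% power the log-rank test needs 57 events (Schoenfeld) to 62 (Freedman).

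**Step 4: is there a variant that reaches 80%?** A one-sided 0.05 test gives 44–46% at 30 per group and 50–52% at 36, across the z-test and Schoenfeld. No standard variant comes close.

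**Step 5: effect detectable at 80% power.** A stronger effect produces fewer FA events, so the event count must be recalculated with the HR.
- 30 per group: HR 0.227 gives FA incidence 1 − 0.625^0.227 = 10.1%. Events are 30 × (0.375 + 0.101) = 14.3, and √14.3/2 × |ln 0.227| = 2.80 = 1.96 + 0.84.
- 36 per group: HR 0.264 gives 11.7%. Events are 36 × (0.375 + 0.117) = 17.7, and √17.7/2 × |ln 0.264| = 2.80.

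Holding events at 17.25 and 20.7 would suggest HR 0.26 and 0.29. At those values simulated log-rank power is only 68% and 70%, so the true requirement is slightly stronger than even the Schoenfeld figures.

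**The case against.** The best defence is that the protocol does not present this as a confirmatory trial. Section 2.1 makes feasibility the objective, and section 2.7 offers the calculation for reference only. Section 2.9.2 drops subgroup analyses because the sample is small, and the Discussion calls the trial a small pilot whose results may not be conclusive. This stands as a reason not to criticise the size of 72, and it means readers get some warning about a null result. It does not rescue the power sentence, which is a statement of fact with all its inputs printed.

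Three stronger readings are tempting, but the document does not support them:
- **That 30 per group was derived from the faulty formula.** The formula does return 30, and section 2.8 speaks of a sample size estimate. But section 2.7 says the 30 was allocated first, so derivation is only an inference. The point does not depend on it.
- **That the dropout allowance is wrong.** As worded, 30 plus 20% is 36, and twice 36 is 72. The text never says that 30 per group remain after 20% of 72 are lost. Dividing by 0.8 (38 per group) is the better convention, but that is a choice. At most one can note that 20% dropout leaves 72 × 0.8 = 57.6, about 58.
- **That the trial needs 4,947 per group.** That applies only to a test of superiority by at least 15 points, and section 2.9.2 does not clearly plan one.

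**Conclusion.** The statement of over 80% power is wrong and should be corrected. At the protocol's own rates and alpha, power for the planned superiority comparison is about 32–34% with 30 per group and 37–40% with 36, less than half the stated figure. About 101–104 evaluable participants per group would be needed for 80%.

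Two assumptions are involved. First, ε is taken as the difference between the stated rates. This explains how 80% arises, but the power figures use only the rates, alpha and group sizes and do not need it. Second, the log-rank figures assume proportional hazards and a common follow-up period for both rates, since section 2.7 gives no time point. The two-proportion figures agree with them without proportional hazards.

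The finding concerns a false statement. It is not a reason to enlarge the trial or to change its analysis.

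**What to change.** In section 2.7:
- Keep 72 participants and the feasibility rationale already there.
- Delete the formula with (ε + δ), the 0.15 margin and the claim of over 80% power.
- State that for 20.0% vs 37.5%, two-sided 0.05, power is about 32–40% across 30 to 36 per group.
- If a detectable effect is wanted, give HR about 0.23 (RA about 10% vs 37.5%) at 30 per group and about 0.26 (about 12% vs 37.5%) at 36, by Schoenfeld with recalculated events. Add that simulation suggests a slightly stronger effect is needed.

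In section 2.8, refer to the feasibility-based target instead of a sample size estimate.

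The cost is rewording one paragraph and one phrase, with no extra participants and no change to the analysis. The downside is a less favourable stated power. The change should be made before results are interpreted, and the article says recruitment is still under way.

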### 2.8 Randomization and blinding

The randomization will be performed via the block randomization method by using the PROC PLAN procedure of SAS V9.4, which is administered by the Key Unit of Methodology in Clinical Research (KUMCR) at the GPHCM. According to the sample size estimate, 72 patients will be included in this study and randomly divided into two groups at a 1:1 ratio. To avoid wasting random numbers, two extra random numbers were added, and the adjusted random number is 74. Once the sample size reaches 72, patient enrolment will cease, even though there might still be unused random numbers at that point. After informed consent is obtained from participants who meet the eligibility criteria, clinicians can access the online random allocation system to procure the allocation results and immediately implement the intervention measures. When multiple patients are randomly assigned on the same day, the application procedure should be performed one by one. The patients, clinicians and investigators of this trial, including study assistants and statisticians, are blinded to the assignment. Unblinding is permitted in an emergency if a SAE occurs or if the intervention must be known for rescue.

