**FIGURE 1 F1:**
[figure not shown]
Production process of the granules.

The placebo was invented and is produced by Tianjiang Pharmaceutical Co., Ltd. It consists of simple ingredients, such as raw materials and excipients, including maltodextrin bitterant and coloring matter (lemon pigment, sunset yellow pigment and caramel pigment). All the materials are of food grade, and no active ingredient is included, which excludes any notable adverse reactions or threats to the health of human beings. FA and the placebo are identical in appearance, including dosage form, aluminum-plastic packaging, and labeling. All participants receive standardized administration instructions stating “The medication has a slightly sweet taste with mild bitterness” to minimize expectation bias.

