#### 2.4.4 Discontinuation criteria, adherence and concomitant therapy

Long-term medications for the treatment of underlying diseases, such as high blood pressure, are allowed. Other symptomatic treatments, such as NSAIDs, may be used if the investigators judge that they will not interfere with the assessment of the study drug. We strictly prohibit glucocorticoids, either oral or topical. All concomitant medications should be recorded in the case report form (CRF).

The trial intervention should be stopped in the following circumstances: if serious adverse events (SAEs) occur; if the patient’s condition deteriorates drastically during the trial and it cannot be ruled out that the change is related to the trial, the study should be terminated, and the necessary treatment measures should be taken for the patient; and if patients withdraw their consent.

The duration of the intervention phase and subsequent follow-up in this study are notably extensive, particularly for participants who are asymptomatic. To improve medication adherence, our approaches encompass the following aspects:

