#### 2.5.2 The primary outcome

The primary outcome is the time to the occurrence of RA. It is defined as the time interval from inclusion to the occurrence of RA. RA occurrence refers to the confirmation of arthritis or synovitis by ultrasound and meeting the 2010 ACR/EULAR RA classification criteria.

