#### 2.9.3 Monitoring

Any adverse events (AEs) that occur during the study period will be reported to the investigators and recorded in the CRFs. In addition to participant self-reports, abnormal laboratory findings, including routine blood tests, urine tests, liver function tests, kidney function tests and pathological electrocardiograms with clinical significance, will be recorded as AEs. AE details, including the time of occurrence, severity, causality with the intervention, actions taken, and AE outcomes, will be observed and assessed. Causalities between AEs and the FA granules will be assessed according to the WHO Uppsala Monitoring Centre System for Standardized Case Causality Assessment^2^. Any severe AEs or serious adverse drug reactions will be addressed promptly to ensure patient safety and will be reported to the principal investigator and the hospital ethics committee in a timely manner.

The trial flowchart is shown in Figure 2, and the schedules and measurements for the participants are listed in Table 2.

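### In an emergency, an SAE permits unblinding even when the allocation is not needed to manage the participant

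*Protocol article*

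**What the plan says.** All references are to the protocol article.

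- **Who is blinded (2.8):** "The patients, clinicians and investigators of this trial, including study assistants and statisticians, are blinded to the assignment".
- **When the blind may be broken (2.8):** "Unblinding is permitted in an emergency if a SAE occurs or if the intervention must be known for rescue".
- **What an SAE does to study treatment (2.4.4):** "The trial intervention should be stopped in the following circumstances: if serious adverse events (SAEs) occur". The rule applies alike to both arms.
- **What is judged afterwards, efficacy (2.5.2):** "RA occurrence refers to the confirmation of arthritis or synovitis by ultrasound and meeting the 2010 ACR/EULAR RA classification criteria". Table 2 schedules the patient and physician global assessments, VAS and HAQ at every visit to week 104, and ultrasound at enrolment and weeks 12, 24, 52, 78 and 104.
- **What is judged afterwards, safety (2.9.3):** "Causalities between AEs and the FA granules will be assessed according to the WHO Uppsala Monitoring Centre System for Standardized Case Causality Assessment".

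**The concern.** A code break is normally justified by need: the treating physician has to know what the participant received in order to treat them. The second ground in section 2.8 says this. The first does not. It allows the code to be opened because an SAE has happened in an emergency, even if management would be the same on either arm.

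Each such opening gives up blinding without helping the participant. Later ratings by the participant and the clinician, the reading of ultrasound, the application of the classification criteria and the attribution of the event to the granules may then be made by people who know the arm. In a double-blind trial with a two-year course and several subjective outcomes, that exposure is worth avoiding when it costs almost nothing to avoid.

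**Working it through.** The plan states no figure on this point, so the check is a reading of the rule against its neighbours.

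**Step 1. Write the rule as a condition.** Let E = an emergency, S = an SAE has occurred, N = the allocation is needed to manage the participant.

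- Rule as written in 2.8: E and (S or N).
- Need-to-know rule: E and N.

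| Within an emergency | Rule as written | Need-to-know rule |
|---|---|---|
| SAE, allocation needed | permitted | permitted |
| SAE, allocation not needed | **permitted** | not permitted |
| No SAE, allocation needed | permitted | permitted |
| No SAE, allocation not needed | not permitted | not permitted |

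The rules differ in one cell only: E and S and not N. If the SAE ground were meant to apply only where the allocation is needed, it would add nothing to the second ground.

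**Step 2. Check the alternative reading.** The opening qualifier could be read as being defined by the two grounds, so that an SAE counts as the emergency. The rule then becomes S or N, which is wider. The disputed cell is permitted on both readings.

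**Step 3. Ask whether an SAE itself requires the code.** Under 2.4.4 an SAE stops the intervention in either arm. The stopping decision therefore does not depend on the allocation. The code could still matter for treating the event, but that case is already covered by N.

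**Step 4. Ask what remains to be assessed after a code break.** Section 2.9.2 keeps everyone who received treatment at least once in the intent-to-treat analysis. Assume that a participant who stops the granules continues the scheduled visits. From Table 2:

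- code opened just after week 12: four visits remain (weeks 24, 52, 78, 104), each with ultrasound and with the global assessments, VAS and HAQ;
- code opened just after week 24: three such visits remain (weeks 52, 78, 104).

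The causality judgement for the SAE itself also remains if it has not yet been made.

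**Step 5. Size.** The number of code breaks in the disputed cell is the number of participants with an emergency SAE for whom the allocation was not needed and the code was opened anyway. The article gives none of these inputs. No figure can be derived.

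**The case against.** **The sentence is narrower than it may look.** It is limited to emergencies, and it permits unblinding without requiring it. A reader might infer that any SAE is enough to open the code. The plain wording does not support that for a non-emergency SAE. This stands, and the point is limited accordingly. It does not remove the disputed cell, since an emergency is not the same thing as a need to know the arm.

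**A condensed article may leave the procedure to other documents.** Section 2.9.1 announces an SOP for the whole team. The order in which unblinding, endpoint assessment and causality assessment take place may be set there, and its absence here is no finding. This also stands. The point concerns the rule that the article does state.

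**The endpoint has objective elements.** It requires ultrasound confirmation and published classification criteria. That limits the scope for bias but does not remove it, because both involve an assessor's judgement. The global assessments, VAS and HAQ have no such protection.

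**Stronger readings that the documents do not support:**

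- *New arthritis would itself be an SAE, so primary events would be unblinded before they are judged.* No section treats arthritis or RA onset as an SAE, and none places endpoint assessment after a code break.
- *Once unblinded, a placebo SAE is unrelated by definition.* Section 2.4.2 does say of the placebo that "no active ingredient is included, which excludes any notable adverse reactions or threats to the health of human beings", but this describes its composition and sets no causality rule. Section 2.9.3 calls for a structured assessment.
- *Reporting would differ by arm.* Section 2.9.3 says "Any severe AEs or serious adverse drug reactions will be addressed promptly to ensure patient safety" and has the same events reported. Severe AEs are therefore reported whatever their cause.

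**Conclusion.** The point holds as a matter of wording. In an emergency, section 2.8 makes an SAE a stand-alone ground for opening the code, including where the allocation is not needed to manage the participant, and section 2.4.4 shows that the stopping decision does not need the code either. The consequence is an avoidable exposure of later ratings and of causality judgements to knowledge of the arm. That is a risk, and no bias is demonstrated.

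Its size cannot be derived. A reader might weigh it by the small number of RA events implied by section 2.7: 36 × (0.200 + 0.375) = 20.7, or 30 × 0.575 = 17.25 without the dropout allowance, so one event is about 5% to 6% of the total. That is only the weight of a single event. It says nothing about how many events would be judged unblinded.

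The conclusion assumes that the sentence in 2.8 is the operative rule and that participants who stop the granules continue follow-up. If the SOP already requires need-to-know, only the published sentence has to be brought into line with it. This is a cheap improvement, not a flaw that threatens the trial.

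**What to change.** 1. **Section 2.8:** reword the sentence so that the blind is broken only when, in the investigator's judgement, knowledge of the allocation is needed to manage the participant. An SAE then leads to unblinding when, and only when, that condition is met.
2. **Section 2.8 or the SOP:** restrict the opened code to those who need it for care, so that the assessors who read the ultrasound and apply the RA criteria stay blinded for that participant.
3. **Section 2.9.3:** have causality judged without using the opened code where feasible. This must not become a step that has to be completed before emergency unblinding; where time does not allow it, care comes first.

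The cost is a few sentences, plus a note by the investigator on why the allocation was needed. Limiting who sees the code takes some discipline at the site. No dose, rescue treatment or stopping rule changes. Section 5 states that recruitment is still under way, so the clarification can protect the assessments still to come.

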### 2.9 Data collection, management, and analysis

#### 2.9.1 Data collection and management

The identification, registration and subsequent follow-up are performed by trained clinicians via questionnaires, physical examinations and laboratory tests. All the investigators and study assistants will attend a training workshop to ensure that they adhere to the study protocol. In addition, a standard operating procedure (SOP) will be prepared and sent to the entire team. Clinical data will be recorded in the CRF by the investigators and will be monitored and reviewed regularly by the data manager and inspectors from the GPHCM Scientific Research Department. The data will be entered by two different operators independently. Archiving and locking occur after two independently entered data points are compared and verified to be error-free. Missing data, suspect data and conflicting data are re-evaluated.

